## Abstract

**Background:**

While cognitive behavioral therapy has shown efficacy in treating stress-related disorders, such as adjustment disorder and exhaustion disorder, knowledge about factors contributing to treatment response is limited. Improved identification of such factors could enhance assessment procedures and treatment strategies. In addition, evaluating how traditional prediction methods and machine learning can complement each other may help bridge gaps in understanding and predicting treatment response.

**Objective:**

This study aims to (1) evaluate putative predictors of treatment response in patients with stress-related disorders using traditional prediction methods and (2) model treatment outcomes using a machine learning approach. This design combines the interpretability of traditional methods with the ability of machine learning to identify complex patterns.

**Methods:**

We will analyze data from a randomized controlled trial comparing 2 internet-delivered treatments, cognitive behavioral therapy versus an active control treatment, for patients diagnosed with adjustment disorder or exhaustion disorder (N=300). Prediction models will be based on pooled data from both treatment arms due to the limited sample size and lack of knowledge on predictors of treatment effects. Putative predictors include sociodemographic and clinical information, clinician-assessed data, self-rated symptoms, and cognitive test scores. The primary outcome of interest is responder status on the Perceived Stress Scale-10, evaluated based on the reliable change index posttreatment. For the traditional approach, univariate logistic regressions will be conducted for each predictor, followed by an ablation study for significant predictors. For the machine learning approach, 4 classifiers (logistic regression with elastic net, random forest, support vector machine, and AdaBoost) will be trained and evaluated. The dataset will be split into training (70%) and testing (30%) sets. Hyperparameter tuning will be conducted using 5-fold cross-validation with randomized search. Model performance will be assessed using balanced accuracy, precision, recall, and area under the curve.

**Results:**

All data were collected between April 2021 and September 2022. We hypothesize that key predictors will include younger age, education level, baseline symptom severity, treatment credibility, and history of sickness absence. We anticipate that the machine learning models will outperform a dummy model predicting the majority class and achieve a balanced accuracy of ≥67%, thus indicating clinical usefulness.

**Conclusions:**

This study will contribute to the limited research on predictors of treatment outcome in stress-related disorders. The findings could support the development of more personalized and effective treatments for individuals diagnosed with adjustment disorder or exhaustion disorder, potentially improving clinical practice and patient outcomes. If successful, this dual approach may encourage future studies with larger datasets and the implementation of machine learning models in clinical settings, ultimately enhancing precision in mental health care.

**International Registered Report Identifier (IRRID):**

DERR1-10.2196/65790

## Introduction

### Background

Mental disorders have a negative effect on quality of life, often precipitating personal suffering and work disability [1]. Around 23% of all who receive a psychiatric diagnosis in Swedish primary care receive a stress-related diagnosis [2], and these account for most psychiatric long-term sickness absences [3]. In Sweden, disorders believed to stem from persistent or overwhelming subtraumatic life events are often categorized using the diagnostic labels adjustment disorder (AD) or exhaustion disorder (ED). Even though ED is only recognized as a medical diagnosis in the Swedish version of the *International Classification of Diseases, Tenth Revision*, the clinical picture of ED is similar to the internationally acknowledged burnout construct [4], a condition that is often associated with significant suffering and work disability [5].

According to diagnostic definitions of AD and ED, these conditions develop in the context of one or several subtraumatic life events (stressors), resulting in mixed symptoms of anxiety, depressed mood, disturbed sleep, fatigue, and impaired memory and concentration. They share symptomatology with other mental disorders, and their diagnostic validity is debated [6,7]. Despite evidence indicating the efficacy of cognitive behavioral therapy (CBT) [8-10] and problem-solving interventions [11] on symptoms of stress, many studies have suffered from significant attrition, and knowledge regarding the factors that contribute to treatment response is still limited [8,12]. Improved identification of such factors could facilitate development of improved assessment procedures and adaptive treatment strategies that might improve outcomes [13].

Research on predictors of psychiatric treatment outcomes is limited [14,15] but demographic factors (eg, age and education level) [16,17], clinical characteristics (eg, use of medication and symptom severity) [17-19], treatment-related factors (eg, treatment credibility and adherence) [16,18] and cognitive functioning [20] have been associated with treatment outcomes.

When it comes to studies investigating predictors of treatment for stress-related disorders, Kocalevent et al [15] found that symptoms of anxiety but not perceived stress, depressive symptoms, or demographic variables predicted self-rated mental health following treatment for patients diagnosed with AD. In a study investigating burnout, Pallich et al [21] identified emotional competence, but not demographic characteristics, as a predictor of treatment response. However, both of these studies suffer from limited generalizability due to their inadequate description of the treatment offered, the fact that the interventions were conducted in an inpatient setting, and the lack of control groups. In ED patients, one study identified several predictors of treatment outcome following multimodal rehabilitation, including younger age, baseline symptom severity (insomnia, anxiety, and depression), perfectionism, physical activity level, treatment credibility, and a history of sickness absence due to ED [22]. However, the effects of demographics and pretreatment symptoms were so small that they offered limited clinical utility. In sum, at the current stage of research, it is a challenge for clinicians to determine who will benefit from treatment, underscoring the imperative for more sophisticated predictive studies.

Traditionally, prediction in psychiatry has relied on interpretable linear or logistic regression models. The aim has been to identify variables explaining a statistically significant portion of the variance in outcome, under the premise that such variables should inform researchers and clinicians. For example, the presence of previous sickness absence and earlier unsuccessful treatment attempts might lead a psychologist to conclude that a patient requires additional support, possibly extending the treatment duration. Although this approach of identifying predictors has offered some clinical utility, it often falls short in practice; the predictive power of specific variables in isolation is typically inadequate to inform assessment, treatment selection, and adaptations of interventions. Given the inherent complexity of mental disorders, the likelihood of pinpointing strong predictors with clinical utility is small, thus limiting the practical value of this approach [23,24].

Machine learning (ML) represents a promising methodological shift in psychiatric prediction modeling, transitioning from the identification of statistically significant predictors to an emphasis on quantifiable model performance, characterized by ensemble methods and adaptability to new datasets. This approach often sacrifices explainability in favor of enhanced predictive performance but offers unique value in handling the complex, nonlinear, high-dimensional data characteristic of mental disorders [25]. With this approach, a model generates a prediction (eg, remission, yes or no) intended to be actionable for a clinician. For example, patients predicted to have low probability of treatment success could be offered additional psychological support or an alternative intervention, thus increasing the likelihood of remission [26,27].

Forsell et al [28] have proposed a balanced accuracy (BACC) threshold of 67% as a benchmark for clinical utility in psychiatric applications, offering a tangible goal for ML implementation. However, the efficacy of ML in this domain remains an ongoing area of inquiry, and its capacity to surpass conventional methods in clinical usefulness is yet to be established [29].

Given the high prevalence and substantial societal costs associated with stress-related disorders, it is imperative to critically evaluate both the applicability and the limitations of ML within this specific context. Such an assessment will not only contribute to the broader understanding of the role of ML in precision psychiatry but also inform the development of more effective diagnostic and treatment strategies for stress-related disorders.

### Objective of the Study

The overall objective of this study is to predict treatment outcomes in patients with stress-related disorders. Due to limitations in existing methods for prediction analyses, this study aims to first evaluate putative predictors using a traditional prediction paradigm, and second to model treatment outcomes using an ML approach. Our primary outcome of interest is responder status after treatment on the Perceived Stress Scale-10 (PSS-10), evaluated using the reliable change index (RCI; further described in the Planned Statistical Analysis and Data Cleaning and Preparation sections). On the basis of earlier research on predictors of treatment outcome, we hypothesize that key predictors will include younger age, education level, baseline symptom severity, treatment credibility, and history of sickness absence. Furthermore, we anticipate that the ML models will outperform a dummy model predicting the majority class and achieve a BACC of ≥67%, thus being indicated clinically useful [28].

## Methods

### Study Design

We will use collected data from a randomized controlled trial (RCT; N=300) of internet-delivered CBT for patients diagnosed with AD or ED compared to an active, internet-delivered control condition consisting of general health-promoting advice. A priori power analysis conducted for the main outcome in the RCT indicated that 300 study participants would be needed for a 90% power to detect a between-group effect size of Cohen *d*=0.4 with a significance level of .05 and an expected attrition rate of 10%. Due to the limited sample size and general lack of knowledge on predictors of treatment effect, prediction models in this study will be based on pooled data from both treatment arms. The study design is prospective, and predictors will include sociodemographic and clinical information, clinician-assessed data, self-rated symptoms, and results from cognitive test scores. The results will be reported in line with the TRIPOD+AI (Transparent Reporting of a Multivariable Prediction Model for Individual Prognosis or Diagnosis+Artificial Intelligence) statement [30].

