#### Treatment

Patients were randomized to one out of two 12-week internet-delivered treatments (CBT and general health-promoting advice). They both consisted of web-based text-based modules with related exercises and assignments. Patients were guided sequentially through the modules by a therapist via a secure web-based platform. The therapists’ primary role was to provide feedback on exercises, support in problem-solving, and to give emotional and technical support via weekly asynchronous text messages. Therapists were licensed clinical psychologists or clinical psychology students in their final year of training. Because this study will not evaluate the individual treatments, they will not be further described here. A full description of the treatments is described in the study by Sennerstam et al [34].

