### Putative Predictors

#### Overview

Predictors were gathered through self-report measures that were administered in the web-based study platform, clinical assessment conducted before inclusion to the study, and remote cognitive testing. Table 1 presents all predictors included in the study.

**Table 1 table1:** Putative predictors of treatment outcome in stress-related disorders

Predictor		Construct measured	Type	Clinician-rated	Scoring range

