**Treatment-related predictors**					
	Clinician treatment expectancy	—	Interval	✓	0-10
	Treatment credibility scale	—	Interval		0-10

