#### Predictor Analysis

For the traditional regression analysis, data will be imputed using the KNN imputer. The imputer, a nonparametric imputation method, works by imputing missing values based on the k-nearest neighbors; in this study *k* will be determined by cross-validation. It uses the Euclidean distance metric to find the nearest neighbors and can be used for both numerical and categorical data. Each missing value is imputed using values from its k-nearest neighbors. After imputation, we will run univariate logistic regressions for each predictor listed in Table 1 using RCI as a target variable. Predictors that are statistically significant in the univariate analyses will then be included in an ablation study, a systematic approach to evaluate feature importance. This method involves iteratively removing each significant predictor from a full model, measuring the change in explained variance, and then reinserting it, thereby quantifying each predictor’s unique contribution to the model’s explanatory power in the context of all other features.

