#### Train Test Split

As the ultimate goal of any model is to predict an outcome in unseen data, the ML models will be developed using a training set, and then evaluated on a test set stratified on main diagnosis (AD or ED) and responder status. In total, 70% of the data will be used for selecting predictor variables and training the models, and 30% for testing the prediction accuracy of the models. The choice of 70 to 30 was due to the limited size of our sample, as fewer observations in the testing data makes it difficult to use uncommon predictors. No external validation set is currently available at the time of writing.

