### Implications for Clinical Practice

The study’s findings could significantly impact clinical practice by contributing to the limited research on predictors of treatment outcome for stress-related disorders. Given the current lack of a gold standard treatment for AD and ED, this research is particularly timely and relevant. The investigation into ML models for treatment outcome prediction may encourage future larger-scale studies and, potentially, the implementation of these models in clinical settings as decision support tools. These could help clinicians tailor treatments by integrating complex data, such as patient demographics, symptom severity, and treatment history, to recommend evidence-based options, guiding therapy selection, and monitoring progress in real time. By operationalizing predictive insights, decision support tools could enhance clinical precision, reduce trial-and-error in treatment, and improve patient outcomes for individuals with stress-related disorders.

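### Randomised arm is left out of the pooled prediction models, so the six week-3 predictors, including treatment credibility, can partly stand in for which treatment was given

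*Protocol article*

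**What the plan says.** Under Treatment, the article reports that "Patients were randomized to one out of two 12-week internet-delivered treatments", namely internet-delivered CBT or general health-promoting advice. Under Study Design it says that "prediction models in this study will be based on pooled data from both treatment arms", and gives the reason: "Due to the limited sample size and general lack of knowledge on predictors of treatment effect".

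The predictor set is closed: "Table 1 presents all predictors included in the study". No row of Table 1 is randomised arm. The block headed "Treatment-related predictors" holds only clinician expectancy and the treatment credibility scale.

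For the traditional analysis (Predictor Analysis), "we will run univariate logistic regressions for each predictor listed in Table 1 using RCI as a target variable". The significant predictors then enter an ablation meant to quantify what each contributes beyond the others. Under Train Test Split, the models are "evaluated on a test set stratified on main diagnosis (AD or ED) and responder status". Arm appears in none of these steps.

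Six predictors are taken 3 weeks into treatment: PSS-10, ISI and the three SMBQ subscales (Outcomes and Table 1), and treatment credibility (Treatment-Related Predictors). Credibility is one of the hypothesised key predictors (Objective of the Study).

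**The concern.** A variable measured after randomisation can be shifted by the treatment received. Credibility is the clearest case. Each patient rates the treatment he or she was assigned, so the two arms are answering about different objects. If one treatment is both more credible and more effective, pooled credibility will be associated with response even if, within each arm, it predicts nothing. The five week-3 symptom scores are exposed in the same way.

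At stake are the interpretation of one named hypothesis and of five other listed predictors, and the ablation's account of each predictor's own contribution. Without arm in the model, a week-3 variable can be credited with arm's share. The random forest importances have the same weakness. The classifiers also forgo a recorded variable that is available when the prediction is made.

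The reasons given for pooling, a limited sample and little knowledge of effect predictors, argue against separate models per arm or many interactions. They do not explain leaving out one binary indicator.

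**Working it through.** **1. The plan's own figure.** Inputs from Study Design: d=0.4, 90% power, significance level .05, 10% attrition. Two-sided testing and 1:1 allocation are assumed. n per arm = 2(1.960+1.282)²/0.4² = 131.3, so 132; the total is 264; 264/0.9 = 293.3, so 294. The t-test version gives 133 per arm, 266 in total and 296 after attrition. Both are close to the stated 300. So d=0.4 is the effect the RCT was sized to detect; the article reports no observed effect.

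**2. From d=0.4 to responder rates.** The responder rate is not given, so 30% in the control arm is assumed.
- Logistic conversion: OR = exp(0.4·π/√3) = 2.07, giving 30% versus 47%.
- Latent normal shift: Φ(Φ⁻¹(0.30)+0.4) = 0.45, giving 30% versus 45% (OR about 1.9).

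**3. Baseline predictors.** Simulation with 270 analysed (300 × 0.9), 30% versus 45%, 2,000 runs, predictor independent of arm:
- type I error 5.7% unadjusted, 5.8% adjusted for arm;
- with a true OR of 1.5 per SD, mean estimate 1.49 unadjusted and 1.51 adjusted, power 0.85 and 0.86.

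Omitting arm does no material harm here.

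**4. Week-3 predictors.** Same set-up, but the predictor differs between arms and has no association with response within arm. Share of studies with p<.05:

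| Arm difference | Rates assumed | Unadjusted | Adjusted |
|---|---|---|---|
| 0.2 SD | 30% v 45% | 5.7% | 5.2% |
| 0.3 SD | 30% v 47% | 7% | 4.4-4.8% |
| 0.4 SD | 30% v 45% | 8.2% | 5.5% |
| 0.5 SD | 30% v 47% | 11% | 4.4-4.8% |
| 0.6 SD | 30% v 45% | 10.6% | 4.8% |
| 0.8 SD | 30% v 45% | 15.3% | 5.1% |
| 0.8 SD | 30% v 47% | 18% | 4.4-4.8% |

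The 45% rows use 2,000 runs and the 47% rows 1,500; for the latter the adjusted range covers all three settings. If the predictor has a real within-arm OR of 1.5, leaving arm out moves the estimate only to about 1.56 (0.3 SD) or 1.59 (0.5 SD).

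**5. Balanced accuracy (BACC).** Classifying by arm alone, at 30% versus 47%: ½(0.47/0.77 + 0.70/1.23) = 0.59. At 30% versus 45%: ½(0.45/0.75 + 0.70/1.25) = 0.58. With a latent shift of d=0.2 it is about 0.54.

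The relevant quantity is the gain over a model that already holds other predictors. With those independent of arm, an arm OR of 2.07 and about 30% control response, adding arm moves BACC from 0.627 to 0.645, from 0.658 to 0.672, and from 0.685 to 0.696. The gain is 0.01-0.02.

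**The case against.** The strongest reply is that pooling is disclosed and justified, that the article says it does not evaluate the individual treatments, and that most predictors precede treatment. Four of the five hypothesised key predictors (age, education, baseline severity, sickness absence) are pretreatment variables, and randomisation protects them. For the machine learning aim, an association that partly reflects arm is still valid prediction. The false-positive figures need both a real treatment effect and a sizeable week-3 difference, and the article documents neither; the comparator is itself an active, therapist-guided programme in the same format. All of this stands, and it limits the point to six predictors and a modest effect. It does not explain the omission of arm, and it does not protect credibility.

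A reader might infer more than the document supports:
- **That all associations are confounded by arm.** Step 3 shows otherwise for baseline variables.
- **That a known driver of outcome is discarded.** No between-arm result is reported; d=0.4 is an assumption.
- **That arm would close about half the gap to 67%.** From 0.50 to 0.58-0.59 is about half of 0.17, but that is arm used alone. Gains in BACC do not add, and the week-3 scores may already carry part of the arm effect.
- **That the article claims these models can choose a therapy.** The phrase "to recommend evidence-based options, guiding therapy selection, and monitoring progress in real time" describes what tools could do after larger studies, and Comparison to Prior Work calls for external validation and implementation trials first. A main effect for arm would not support treatment selection anyway; that needs interactions.
- **That a split not stratified by arm is a flaw.** A random split balances arm in expectation, and no harm from it has been shown.

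**Conclusion.** The point holds in limited form and should be fixed. Arm is absent from the predictor list, the regressions and the ablation, and the stated rationale does not cover that. The consequence is confined to the six week-3 predictors, of which treatment credibility matters most because it is a named hypothesis. Under a true d=0.4 and no within-arm association, the nominal 5% error is about 5-6% at an arm difference of 0.2 SD and about 8-18% at 0.4-0.8 SD; adjustment restores about 5%. The loss of predictive information is likely to be about 0.01-0.02 in BACC.

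These sizes rest on 1:1 allocation, 270 patients analysed, a control responder rate of about 30%, and week-3 arm differences that the article does not give. If the treatments barely differ in effect, or the week-3 variables barely differ by arm, the practical effect is small.

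**What to change.** Keep the pooling, and:

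1. Add randomised arm to Table 1 and to all four classifiers.
2. Fit the logistic regressions as predictor plus arm, at least for the six week-3 predictors. For baseline predictors this is harmless but not needed.
3. Keep arm in every ablation model, so that each predictor's contribution is judged given arm.
4. Describe the findings as prognostic across both arms.

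Stratifying the split by arm is optional. If arm is to stay out, the article should say why.

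The cost is one variable already recorded and one degree of freedom per model, with no change to the sample size. The article states that the data had not been analysed for this study as of March 2025, so at that date the change could still be specified in advance.
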